## Abstract

**Clinical trial registration:**

Study Protocol Registration details: China Clinical Trial registration number ChiCTR2500101576.

## Introduction

1

Secondary school students are currently facing increasingly complex psychological stress (Pascoe et al., 2020). The intensification of social competition, the widespread phenomenon of educational involution, and the unique aspects of adolescent physical and mental development have made psychological stress a significant issue impacting their healthy growth and well-being (Wang et al., 2024). According to the World Health Organization, 2022 report, approximately 14% of adolescents aged 10 to 19 worldwide experience varying degrees of mental health issues. The primary triggers identified include academic pressure, family expectations, and social anxiety (Varzaneh et al., 2024).

Additionally, the Ministry of Education’s 2023 Blue Book on Youth Mental Health in China reveals that over 60% of secondary school students report experiencing moderate or higher levels of psychological stress, with this percentage showing a significant upward trend during critical promotional stages (Fu et al., 2021). This situation not only threatens the mental well-being of individuals but can also lead to a range of negative outcomes, such as academic burnout, strained interpersonal relationships, and crises of self-identity (Liu and Wang, 2024). Ultimately, these issues may have far-reaching implications for broader social development.

Traditional interventions for adolescent psychological stress typically focus on psychological counseling or pharmacotherapy. Psychological counseling offers several advantages: it addresses underlying issues, avoids drug-related side effects, and promotes self-awareness and improved interpersonal relationships (Tareke et al., 2023). However, this approach often requires longer treatment cycles, relies heavily on professional guidance, and can be more costly (Kiriakaki et al., 2022). In contrast, pharmacological therapies provide rapid symptom relief, are convenient to administer, and are widely applicable (Alorfi, 2023). Nevertheless, they have notable drawbacks, including potential side effects, limited focus on the root causes of mental health issues, and the risk of drug dependence (Sibley et al., 2023).

In recent years, a growing body of research has shown that moderate physical exercise can significantly reduce psychological stress (Mahindru et al., 2023). Through participation in sports activities, adolescents can effectively regulate their emotions, relieve anxiety and depression (Martinez et al., 2024), and find healthy outlets for emotional expression. Engaging in sports also helps build self-confidence and fosters resilience and courage in the face of challenges (Husain et al., 2024). On a social level, sports provide valuable opportunities for peer interaction and collaboration, thereby enhancing key social skills such as communication, teamwork, and leadership (Fernandez-Rio and Casey, 2021). Moreover, physical activity has been shown to improve cognitive functions in young people, including attention, memory, and decision-making (Latino and Tafuri, 2024). It also promotes the adoption of a healthy lifestyle, encouraging balanced nutrition and a regular daily routine.

Given the high academic pressure and limited time available for physical activity among Chinese secondary school students (Zhu et al., 2021), we have developed a time-efficient, TABATA-style high-intensity interval training (HIIT) module. TABATA training, recognized for its effectiveness in neuroendocrine regulation and minimal time requirements (Tabata, 2024), may be particularly well-suited for adolescents with demanding academic schedules. This method involves 20 s of high-intensity exercise followed by 10 s of rest, repeated for a total of eight cycles. It has been shown to enhance endorphin secretion and improve executive functioning (Tabata, 2022). However, the underlying mechanisms by which this training regulates psychological stress, as well as its feasibility and efficacy in adolescent populations, warrant further investigation. The primary objective of this study is to assess the feasibility and acceptability of the TABATA training module we have developed as an intervention to reduce psychological stress among Chinese adolescents. The secondary objectives are to evaluate changes in psychological stress level, physical fitness, academic performance, and quality of life.

## Materials and methods

2

### Study design

2.1

This is a two-stage, mixed-methods study comprising an initial feasibility randomized controlled trial (RCT), followed by a qualitative study. The reporting of this protocol will adhere to the SPIRIT guidelines. This study will be conducted in secondary schools in Nanjing City, Jiangsu Province, China. The research protocol received its primary ethical review and approval from the Ethics Committee of Nanjing Normal University (Approval Number: NNU202407008; Date: July 2024), which holds the principal oversight responsibility for ensuring full compliance with all applicable Chinese laws and regulations, including specific provisions for the protection of minors. Approval from the Universiti Kebangsaan Malaysia Research Ethics Committee (JEP-2024-544) was obtained subsequently by the project lead (a UKM doctoral candidate) for institutional academic purposes, contingent upon the primary approval from Nanjing Normal University. Consequently, all research activities will be carried out under the supervision and in accordance with the requirements of the Nanjing Normal University Ethics Committee. This study was also approved by Nan Hang Secondary School in October 2023. Upon verbal agreement, informed consent and assent forms will be obtained from parents and children, respectively.

### Sample size

2.2

According to Whitehead et al. (2016) recommendations for pilot study sample sizes, to ensure the subsequent main trial achieves 90% power and a two-tailed 5% significance level, the sample size for each group in the pilot study should be set based on the expected effect size: a very small effect (0.1) corresponds to 75 participants, a small effect (0.2) to 25 participants, a medium effect (0.5) to 15 participants, and a large effect (0.8) to 10 participants. Furthermore, Dworkin (2012) noted in theory-based qualitative research that a sample size of 25–30 participants is typically required to achieve theoretical saturation and information redundancy. Integrating these recommendations from both statistical and qualitative research, this study sets the sample size per group at 25–30 participants. This aims to ensure sufficient statistical power while adequately capturing key experiences and feedback during the intervention process.

### Eligibility criteria

2.3

The inclusion criteria are secondary school students in Nanjing, Jiangsu Province, aged 12 to 15 years, who are experiencing moderate to severe psychological stress as identified by the Chinese version of the DASS-21 questionnaire.

Exclusion criteria include students who are unable to participate in physical activity, have a diagnosed mental illness, or are unable to provide informed consent.

### Recruitment and randomization

2.4

The participants in this study will be middle school students in Nanjing, Jiangsu Province, who are experiencing psychological stress. During the selection stage, students will complete the Chinese version of the DASS-21 questionnaire on a large scale through their school’s IT classes. Students with stress scores exceeding 19 will be identified as potential participants.

This study will employ a cluster randomized design. After obtaining informed consent, eligible participants will be grouped by their respective schools. All participants from one school will be assigned to the intervention group and receive the uniform intervention during the specified period. All participants from the other school will be assigned to the control group, maintaining their routine learning and daily activities without any intervention. During the evaluation process, outcome assessors will be blinded to ensure they remained unaware of the group assignments. This design is intended to minimize disruptions to regular teaching activities while ensuring participant privacy and safeguarding against potential stigmatization. Additionally, it helps prevent contamination between intervention and control groups, thereby preserving the study’s internal validity.

Given that the participants were minors experiencing psychological stress, strict measures were taken to ensure their privacy. All personal identifiers were removed from the transcribed data, and code numbers were used in place of participant names. Transcription files were encrypted and stored on a password-protected, stand-alone device, while physical materials were secured in a locked filing cabinet accessible only to the research team. All raw data were securely destroyed within 10 years of the study’s completion.

Participants in the intervention group will undergo 8 weeks of TABATA training, while those in the control group will not receive any intervention or participate in any interviews. Table 1 outlines the participant recruitment timeline, key milestones, and scheduled assessment activities. Stage 2 will involve the qualitative phase of the study. Participants for this phase will be selected from the intervention group in Stage 1. Individual interviews will be conducted with a subset of students who received the intervention, as well as with PE teachers who delivered the training. The aim of this phase is to evaluate the feasibility and acceptability of the TABATA training module.

**Table 1 tab1:** SPIRIT (Standard Protocol Items: Recommendations for Interventional Trials) schedule of enrolment, interventions, and assessment.

Timepoint	Study period										
	Enrolment	Allocation	Post-allocation								Close-out
	9/2025–10/2025	9/2025–10/2025	Week 1	Week 2	Week 3	Week 4	Week 5	Week 6	Week 7	Week 8	12/2025
Enrolment											
Screening	✓										
Eligibility screen	✓										
Informed consent	✓										
Allocation		✓									
Interventions											
Intervention A											
Control											
Assessments											
DASS-21 Chinese version		✓				✓				✓	
Quality of life scale for children and adolescents (QLSCA) Chinese version		✓				✓				✓	
Physical fitness performance		✓				✓				✓	
Blood pressure		✓				✓				✓	

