#### Randomized controlled trials

2.5.1

The TABATA training module is specifically designed for secondary school students experiencing psychological stress. Its aim is to reduce stress among them. This training method is characterized by its high efficiency and time-saving structure.

An eight-week intervention will be implemented, consisting of three sessions per week. This schedule is informed by an analysis of adolescents’ motivations, barriers, and preferences. The intervention will be delivered by physical education (PE) teachers at each participating school. A flowchart outlining the intervention process is presented in Figure 1.

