### Data analysis

2.9

The analysis will focus on obtaining descriptive statistics and confidence intervals for the variables. Participants will be characterized by means, standard deviations, and ranges for quantitative variables, as well as counts and proportions for categorical variables. Since this is a feasibility study primarily aimed at testing our ability to collect data, we will not use data interpolation to address any missing data. Based on the proposal for the pilot study, we have set the following feasibility goals: within 1 month, the intervention group and the control group will each recruit 20 to 30 participants; achieving a recruitment rate of over 70% in the TABATA intervention group; ensuring that more than 80% of students in the TABATA training group complete the 8-week intervention; having more than 70% of adherence rate; and maintaining an overall missing data rate of less than 10%.

All interviews will be recorded using an Apple mobile phone and transcribed verbatim, followed by manual proofreading using Flying Book of Notes software. To gain a comprehensive understanding of participants’ perceptions, an inductive analysis approach will be employed to identify broader themes (Azungah, 2018). Data will be analyzed using NVivo 12 qualitative analysis software to extract key themes related to feasibility and acceptability.

To enhance the credibility and reliability of the findings, researcher triangulation will be used to minimize researcher bias and strengthen the overall robustness of the study (Natow, 2020). First, one member of the research team will input the transcribed data into NVivo 12 and conduct initial coding in collaboration with another team member, merging codes to form preliminary themes. Next, two additional researchers will review the coding and refine the thematic structure for further integration.

Inter-rater reliability will be assessed by calculating the Kappa coefficient using NVivo 12. A Kappa value greater than 0.75 will be considered acceptable, indicating high consistency and data validity. Finally, all members of the research team will convene to finalize the themes related to the feasibility and acceptability of the TABATA training module.

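### With one school per arm, treatment is fully confounded with school, so stage 1 cannot support the randomised comparison or the internal validity that the protocol claims for it

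*Protocol article*

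**What the plan says.** Section 2.1 (Study design) describes a two-stage study "comprising an initial feasibility randomized controlled trial (RCT), followed by a qualitative study". Section 2.4 (Recruitment and randomization) adds: "This study will employ a cluster randomized design". The same section then gives the allocation: "All participants from one school will be assigned to the intervention group and receive the uniform intervention during the specified period", while everyone recruited from the other school is a control without intervention. It argues that this arrangement prevents contamination, "thereby preserving the study’s internal validity", and says that "outcome assessors will be blinded to ensure they remained unaware of the group assignments".

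Section 2.5.1 says of delivery: "The intervention will be delivered by physical education (PE) teachers at each participating school".

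Section 2.2 sets 25–30 students per group and gives adequate statistical power as one of its aims. Section 2.9 says: "The analysis will focus on obtaining descriptive statistics and confidence intervals for the variables". Table 3 lists the primary outcomes (recruitment, retention, adherence, missing data). Table 4 lists the secondary outcomes, mainly pre-to-post changes in DASS-21 stress, QLSCA, fitness and academic ranking. No between-arm contrast is defined.

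**The concern.** A cluster-randomised comparison draws its validity from the number of clusters, not the number of students. With one school per arm, any difference between the schools in PE teaching, exam calendar or intake is also a difference between the arms, and no analysis can separate the two. The words randomised and internally valid describe properties that this design does not have.

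The risk lies in how the secondary results will be read. A control school is followed, Table 1 schedules repeated DASS-21, QLSCA and fitness assessments, section 2.9 promises confidence intervals, and section 2.2 speaks of power. Together these invite a reader, or the authors, to set the two schools side by side and treat the difference as randomised evidence on TABATA, when a school difference alone could produce it.

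Two statements in the same part of the protocol add to this. Assessor blinding does not protect outcomes that students report about themselves while knowing whether they train. The delivery sentence in 2.5.1, read literally, has the intervention given in the control school too.

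**Working it through.** **Number of clusters.** Section 2.4 names one intervention school and one control school, so k = 1 school per arm. Cluster-level degrees of freedom for the arm difference are 2(k − 1) = 2(1 − 1) = 0. Between-school variance cannot be estimated, and an interval could be formed only by importing an ICC from outside. The first positive value is at k = 2 (2 df, t = 4.30). None of this needs an assumption.

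**The plan's own figure.** The 25–30 per group in section 2.2 is taken from a lookup (25 for an effect of 0.2) combined with a qualitative saturation range (25–30). It is not the output of a formula, so there is nothing to recompute. It counts students and contains no ICC or design effect.

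**Illustration of a student-level comparison.** Inputs: m = 25 or 30 students per school (section 2.2); two-sided 5% level, which section 2.2 mentions for the main trial; ICC assumed at 0.01 and 0.05, because the document gives none. If there is no treatment effect:

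- Variance ratio R = [ICC + (1 − ICC)/m] / [(1 − ICC)/m]
- Actual type I error = 2·P(t > t₀.₉₇₅/√R), with 2m − 2 df

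Worked case, m = 25 and ICC 0.05: R = (0.05 + 0.038)/0.038 = 2.32. With 48 df, t₀.₉₇₅ = 2.01, and 2.01/√2.32 = 1.32, which gives 19.3%.

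| ICC (assumed) | m | R | Type I error | Coverage of nominal 95% interval |
|---|---|---|---|---|
| 0.01 | 25 | 1.25 | 7.9% | 92.1% |
| 0.01 | 30 | 1.30 | 8.5% | 91.5% |
| 0.05 | 25 | 2.32 | 19.3% | 80.7% |
| 0.05 | 30 | 2.58 | 21.8% | 78.2% |

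Simulation with 40,000 replicates gave 7.9% (m = 25, ICC 0.01), 19.4% (m = 25, ICC 0.05) and 21.7% (m = 30, ICC 0.05). Section 2.9 gives a recruitment goal of 20–30 per group; at m = 20 the type I error is 7.3% and 16.6% for the two ICCs.

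**More students do not help.** At ICC 0.05 and m = 30, the naive half-width is 1.96·√(2·0.95/30) = 0.49 SD. Including school variance it is 1.96·√(2·(0.05 + 0.95/30)) = 0.79 SD. However large m becomes, it cannot fall below 1.96·√(2·0.05) = 0.62 SD. The naive interval keeps its coverage only if the ICC is exactly 0, which two schools cannot verify.

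**Blinding.** Sections 2.7.1 and 2.7.2 describe DASS-21 and QLSCA as self-report instruments. Students in the intervention school know that they train three times a week. The blinding sentence concerns assessors, so it can protect only what an assessor measures.

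**Delivery.** Section 2.5.1 has PE teachers at each participating school deliver the intervention; section 2.4 leaves one of the two schools untreated. Both cannot be literally true.

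**The case against.** The strongest reply is that this is a feasibility study and that the analysis under criticism is not in the plan. That is largely right. Section 2.9 and Table 4 name no between-arm test, interval or efficacy statement, so the error rates above describe a comparison that the design invites, not one that is written down. The primary outcomes need no arm contrast: retention is defined in the TABATA group only, and acceptability comes from interviews with the intervention school's students and teachers.

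Table 4 also uses changes, from which stable school differences such as intake level drop out. What remains is a school-by-time difference, for example in the exam calendar. The ICC of change scores may be lower or higher than the values assumed, so the percentages are illustrative.

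The internal-validity phrase is tied to contamination, and school-level allocation does address that threat, along with the disruption and stigma that section 2.4 mentions. But removing one threat does not make an arm comparison valid when treatment and school coincide.

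The wording about each participating school may simply be loose, since sections 2.4 and 2.4's account of the control group make plain that controls receive nothing. It still needs reconciling.

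A reader might go further and infer that the study is not randomised at all, because no random step is described. The document does not establish this: section 2.4 calls the design cluster randomised, and an article may leave the mechanism to the full protocol. The defect is the same whether or not the school was drawn at random.

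**Conclusion.** The point holds. Stage 1 has one cluster per arm, so treatment and school are inseparable and the cluster-level degrees of freedom are 0. That conclusion rests on the allocation stated in section 2.4 alone, and no analysis plan can repair it. The randomised-comparison label and the internal-validity claim should not stand as written.

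The size of the problem in a student-level comparison depends on an ICC that the document does not give: about 8% false positives at ICC 0.01 and 19–22% at ICC 0.05, with 25–30 students per school, and possibly different for change scores.

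Two stronger readings are not supported. The protocol does not plan an invalid between-arm test; it leaves room for one. Nor does the feasibility aim fail: the primary rates remain estimable, with the limit that retention and adherence reflect a single intervention school.

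**What to change.** - **Sections 2.1 and 2.4:** describe stage 1 as a two-school controlled feasibility study with one cluster per arm, and say that it cannot support a randomised comparison. This wording is accurate whether or not the treated school was drawn at random.
- **Section 2.4, validity:** remove the internal-validity claim, or limit it to the prevention of contamination.
- **Section 2.9:** state that changes in DASS-21, QLSCA, fitness and academic results are reported descriptively by school, with within-school intervals only and no between-arm interval, test or efficacy statement.
- **Section 2.4, blinding:** restrict the claim to outcomes measured by an assessor, and acknowledge that DASS-21 and QLSCA are self-reported by students who know their arm.
- **Section 2.5.1:** reconcile the delivery sentence with the untreated control school in section 2.4.

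These changes are wording and reporting only, with no extra participants, schools or data. The price is a weaker claim: the study will speak to feasibility and acceptability and will describe change within each school, but it will not estimate an effect of TABATA against control.

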### Interventions

2.5

#### Randomized controlled trials

2.5.1

The TABATA training module is specifically designed for secondary school students experiencing psychological stress. Its aim is to reduce stress among them. This training method is characterized by its high efficiency and time-saving structure.

An eight-week intervention will be implemented, consisting of three sessions per week. This schedule is informed by an analysis of adolescents’ motivations, barriers, and preferences. The intervention will be delivered by physical education (PE) teachers at each participating school. A flowchart outlining the intervention process is presented in Figure 1.

**Figure 1 fig1:**
[figure not shown]
Consolidated standards of reporting trails 2010 flow diagram.

The exercise intervention will be structured into three components:

An 8-min warm-up jogAn 8-min TABATA training sessionA 4-min relaxation and stretching cooling down

#### Warm-up jog

2.5.2

The warm-up jog serves as a vital preparatory phase that promotes both physical and psychological readiness (Marakushyn et al., 2024). Light, sustained jogging gradually increases muscle temperature, enhancing the elasticity and flexibility of muscle fibers while improving the speed and strength of muscle contractions. It also boosts blood circulation, ensuring an adequate supply of oxygen and nutrients for the upcoming workout, and facilitates the removal of metabolic waste. These physiological effects help significantly reduce the risk of sports-related injuries such as muscle strains and joint sprains (Bushman, 2024).

In addition to its physical benefits, the warm-up jog stimulates the nervous system, improving reaction time and coordination, thereby enhancing focus and performance during the main workout. Psychologically, it helps reduce anxiety, build confidence, and mentally prepare students for the challenges ahead (Temaj et al., 2024).

